### Sample size calculation

The sample size was estimated based on the results of a study on the changes in the short form Leeds Dyspepsia Questionnaire (SF-LDQ) in response to a 4-week acupuncture intervention versus moxibustion intervention, which showed a mean improvement of the SF-LDQ was − 5.62 ± 2.81 (mean ± SD) in the acupuncture group and − 3.56 ± 2.62 in the moxibustion group respectively [25]. It provides an effect size (Cohen's *d* = 0.758) to estimate the sample size of this study. To achieve 90% statistical power (*α* = 0.05), at least 76 participants are needed. Besides, assuming a 20% attrition rate, ninety-two participants (46 participants per group) will be recruited to detect a two-sided significant difference. The sample size calculation steps are shown in Supplementary file 4.

According to previous fMRI-based studies [26, 27], thirty subjects or more can notably improve the reliability of results. Considering the dropout rate or loss of data due to head motion during fMRI scanning, in this study, thirty-six participants in each group will be randomized to fMRI scans.

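### The stated 92 patients cover about 17% attrition, not the 20% assumed; at 20% about 74 remain against a stated minimum of 76, and power is about 89% instead of 90% (minor)

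*Protocol article*

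**What the plan says.** The section on sample size calculation in the protocol article takes the change in SF-LDQ after 4 weeks from one cited study. The mean improvement (printed there with a minus sign) was "5.62 ± 2.81 (mean ± SD) in the acupuncture group" and "3.56 ± 2.62 in the moxibustion group respectively". From these it derives the planning effect: "It provides an effect size (Cohen's *d* = 0.758) to estimate the sample size of this study". The requirement follows: "To achieve 90% statistical power (*α* = 0.05), at least 76 participants are needed". The attrition step then gives the recruitment target: "Besides, assuming a 20% attrition rate, ninety-two participants (46 participants per group) will be recruited to detect a two-sided significant difference". The section refers the reader to Supplementary file 4 for the steps; that file is not among the documents at hand.

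Two other places bear on the point. The sections on withdrawal and on clinical data analysis say that analyses are by intention to treat and that information from patients who drop out will be used. Table 1 schedules the SF-LDQ at baseline, at the end of treatment and at the end of follow-up, with no assessment in between.

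**The concern.** An attrition allowance exists so that the number remaining after the assumed loss still meets the requirement. Here three figures stand side by side: 76 needed, 20% lost, 92 recruited. Any two of them fix the third, and the printed third does not match. A reader who takes the section at face value will believe that the trial keeps its 90% power through a 20% loss. At stake is the accuracy of the power statement for the primary outcome, and whether the shortfall is large enough to matter for the trial.

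**Working it through.** **Inputs**, all from the sample size section: mean improvements 5.62 (SD 2.81) and 3.56 (SD 2.62); d = 0.758; α = 0.05, two-sided; power 90%; attrition 20%; 92 recruited, 46 per group. Allocation is 1:1.

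**Step 1: reproduce the effect size.** Pooled SD = √((2.81² + 2.62²)/2) = √((7.896 + 6.864)/2) = 2.717. The difference is 5.62 − 3.56 = 2.06, so d = 2.06/2.717 = 0.758. This agrees with the protocol.

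**Step 2: reproduce the 76.** A two-sided two-sample t-test (noncentral t) with d = 0.758, α = 0.05 and power 0.90 needs 37.56 per group, so 38 per group and 76 in total. This agrees. The alternatives do not give 76: the normal approximation gives 37 per group (74 in total), and a one-sided t-test gives 31 per group. The two-sided t-test is therefore the yardstick for the rest.

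**Step 3: the attrition step.** To keep n patients after losing a fraction a, recruit n/(1 − a).

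- In total: 76/(1 − 0.20) = 95.
- Per group: 38/0.80 = 47.5, so 48 per group and 96 in total.
- The stated figure: 76 × 1.2 = 91.2, rounded up to 92; per group 38 × 1.2 = 45.6, rounded up to 46. Both printed numbers match a multiplier of 1.2.

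**Step 4: what 92 delivers.** At 20% loss, 92 × 0.80 = 73.6, or 36.8 per group: 2 to 3 patients short of 76. The largest loss that still leaves 76 is 1 − 76/92 = 17.4%.

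**Step 5: power by the two-sided t-test at d = 0.758**, assuming that patients who drop out contribute nothing to the primary outcome:

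| Evaluable per group | Situation | Power |
|---|---|---|
| 46 | no loss | 94.9% |
| 38 | the stated requirement | 90.3% |
| 37 | 74 evaluable | 89.6% |
| 36.8 | exactly 20% loss | 89.4% |
| 37 and 36 | 73 evaluable | 89.1% |

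Against the 90% target the deficit is 0.4 to 0.9 percentage points.

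**The case against.** The strongest objection is that this is too small to matter. That is largely right. The shortfall is 2 to 3 evaluable patients and less than one point of power. By the normal approximation, 37 per group still gives 90.3%, although that method would have given 74 as the requirement, not the 76 printed. The planning effect is also less certain than this error is large: with all 76 patients evaluable, power is 89.7% at d = 0.75 and 88.9% at d = 0.74. This settles the severity, but it does not make the three figures agree.

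A second objection is that under intention to treat nobody is lost, and with all 92 analysed the power is 94.9%. This helps only in part. The section itself allows for attrition, so it treats dropouts as lost information. With no SF-LDQ between baseline and the end of treatment, a patient who leaves during treatment has no scheduled post-baseline value of the primary outcome to contribute. What stands is that the 89% is conditional: it assumes that dropouts supply no primary outcome data.

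Three stronger readings are tempting, and the documents do not support them.

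- A reader might infer that the trial is underpowered. It is not in any material sense at the planned effect.
- A reader might take it as established that the authors multiplied by 1.2. The match is exact in total and per group, but the steps are in a file not shown. The inconsistency does not depend on how 92 was reached.
- A reader might put the power lower still because the analysis section allows the Mann-Whitney test. The usual efficiency discount for that test against the t-test applies to normal data, whereas the test would be chosen here when the data are not normal, and its relative efficiency can then exceed 1. No such figure belongs in this point.

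**Conclusion.** The inconsistency is real and visible within one section: 76 needed, 20% attrition and 92 recruited cannot all hold. At 20% attrition about 74 patients are evaluable; 92 protects the 76 only up to 17.4% attrition; and 95, or 96 with equal groups, would be needed to match the stated assumption. The power consequence is about 89% instead of 90%. This rests on a two-sided t-test, d = 0.758 and no primary outcome data from dropouts; any data they do supply would shrink the gap. The required size of 76 and the effect size calculation are correct. Severity is minor: a stated figure needs correcting, and neither the design nor the analysis has to change because of it.

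**What to change.** Correct the statement that follows "at least 76 participants are needed". It could read: 92 randomised patients (46 per group) allow for about 17% attrition at 90% power; with 20% attrition about 74 would be evaluable and power would be about 89%, if dropouts provide no primary outcome data. Check that Supplementary file 4 agrees, and align it if it does not. The cost is a short text change and a slightly less favourable figure. Recruiting 96 (48 per group) would instead make the 20% statement true, at the cost of four more patients; given the size of the gap this is optional.

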### Interventions

Participants in both groups will receive 20 sessions of acupuncture or moxibustion treatment in 4 weeks. Five times per week on *Zhongwan* (CV-12) and *Zusanli* (ST-36) will be selected as the treatment acupoints, which are the most commonly used acupoints for FD [28]. The locations of the acupoints are shown in Fig. 2A and Supplementary Table 1. All treatments will be performed by two acupuncturists. With at least 3 years of clinical experience and certified a 2-day standard training course.

**Fig. 2 Fig2:**
[figure not shown]
**A** Location of acupoints (CV-12 and ST-36). **B**
*Hwato* acupuncture and brief acupuncture manipulation steps. **C**
*Aikeshu* moxibustion stick and brief moxibustion manipulation steps

#### Acupuncture intervention

After skin sterilization, the sterile needles (40 mm × 0.25 mm; Suzhou Medical Co., Ltd., China) (Fig. 2B) will be inserted perpendicularly into the acupoints (CV-12 and unilateral ST-36) with a depth of 25 to 30 mm. Then, the needle will be twisted between 90 and 180°, be lifted and thrust in an even amplitude between 3 and 5 mm, 60 times to 90 times per min to obtain the *deqi* sensation (*a special sensation of acupuncture*). The needles will be retained in the acupoints for 30 min, and the aforementioned manipulation will be applied every 10 min.

#### Moxibustion intervention

The lightened moxibustion sticks (13±1g; 60mm × 4.1mm; Bozhou Aikeshu Medical Co., Ltd., China) (Fig. 2C) will be placed on both CV-12 and unilateral ST-36. During the period of moxibustion, the temperature of the portable moxibustion will be adjusted according to the patient’s tolerance to prevent skin scald.

The *deqi* phenomenon is a special sensation of acupuncture and moxibustion, and it is closely related to clinical efficacy [29, 30]. The *deqi* sensation will be evaluated by the Chinese version of modified Massachusetts General Hospital Acupuncture Sensation Scale (C-MASS) [31], and the *deqi* sensation of moxibustion also will be evaluated by the C-MASS-based 10-point visual analog scale (VAS) form. Patients will self-assess the sensations by this scale. The sensation of acupuncture and moxibustion will be measured after the 1st and 20th interventions, respectively.

#### Concomitant treatments

If the symptoms are unbearable and FD patients have to take drugs (i.e., *Gastrointestinal motility regulating drugs*, *proton pump inhibitors*, *Chinese medicine*, etc.), participants need to tell us the time to take, dosage, and the specific information about the drugs, or any other therapy. Finally, we will record the details of the treatment in the case report form.

### Outcome measurements

The outcome measurements including (Table 1) the SF-LDQ, the Nepean Dyspepsia Index (NDI), the Symptom Index of Dyspepsia (SID), the Zung Self-Rating Anxiety Scale (SAS), and the Zung Self-Rating Depression Scale (SDS). Moreover, the evaluation time of these measurements was presented in the Table 1.

#### Primary outcome measurements

Our primary outcome is the improvement of SF-LDQ after 4 weeks of treatment. The SF-LDQ is a validated and reliable tool to measure the frequency and severity of five dyspeptic symptoms (epigastric pain, postprandial fullness, indigestion, epigastric burning, and postprandial nausea) [32]. Graded on a 5-point Likert scale, the higher the score of the five symptoms, the more severe the disorder.

#### Secondary outcome measurements

The secondary outcomes contain the NDI, the SID score, the SAS, and the SDS. Among them, NDI is a commonly used questionnaire to assess upper gastrointestinal symptoms and QoL of patients [33]. It includes two parts: symptom checklist (NDSI) and QoL questionnaire (NDQLI). A higher score of NDI indicates milder symptoms and better QoL. SID focuses on the 4 chief symptoms of FD (epigastric pain, burning, postprandial fullness, and early satiety) [34]. Using a 4-point Likert scale, the dyspeptic symptoms will be graded from 0 (none) to 3 (sever), and the total score will be used to evaluate the severity of dyspepsia [35]. The SAS and the SDS will be selected to evaluate the psychosocial state of FD patients [36, 37].

#### Heart rate variability test

The autonomic nervous system (ANS) plays a role in the physical function and pathological change of the digestive tract [38]. Dysfunction of the ANS may be an essential factor for the development of FD [39]. Heart rate variability (HRV) is a sensitive, quantitative, and intuitive indicator for the non-invasive assessment of autonomic nervous activity [40]. The 24-h dynamic electrocardiogram (ECG) (CT-086S, BENEWARE Co., Ltd., China) will be used to assess the HRV of patients. The metrics of HRV include the standard deviation of NN intervals (SDNN), the standard deviation of sequential 5-min RR interval means (SDANN), and the root mean square successive difference (RMSSD), etc. HRV will be measured after randomization and the 20th treatment.

### MRI scan

The fMRI data will be acquired with the Siemens 3.0T MRI (Siemens, Munich, Germany) at the Imaging Center of the fifth Chengdu Hospital, Sichuan, China. A 3-dimensional MRI sequence will be used to gain the high-resolution structural image. The parameters as following: repetition time/echo time = 1900 ms/2.26 ms, slices = 176, data matrix = 256 × 256, field of view = 256 × 256 mm^2^, and slice thickness = 1 mm. The parameters of blood oxygenation level-dependent resting-state functional image will be set as follows: repetition time/echo time = 2000 ms/30 ms, flip angle = 90°, slices = 30; data matrix = 64 × 64, field of view = 240 × 240 mm^2^, slice thickness = 5 mm, total volume = 240, and total scan time = 480 s. Twenty-four hours before scanning, every patient will be asked to keep their regular lifestyle, avoid staying up late, smoking, and drinking coffee or tea. Before scanning, every patient will stay at a restroom for 30 min and keep calm without thinking. During scanning, patients will be required to keep their eyes closed and ears plugged.

### Patient safety

Safety monitoring will be executed strictly throughout the study with reporting for adverse events (AEs) and serious adverse events (SAEs) such as subcutaneous hemorrhage, vertigo, infection, and burn and scaled injures. AEs/SAEs will be handled properly, recorded carefully, and report the SAEs and treatment to the principal investigator and the Ethics Committee immediately. We will pay all medical fees. Additionally, free medical and psychological consultation will be provided until they recover from AEs/SAEs.

### Data management

Clinical data will be managed with printed case report forms and electronic data capture (EDC). An independent data administrator will keep the data. Only principal investigators have the access to the full dataset and will perform double-data entry. The evidence-based medicine center of the CDUTCM is responsible for monitoring the study and data every 3 months and will make the final decision to terminate the trial. We will publish our results in peer-reviewed journals.

### Data analysis

#### Clinical data analysis

All analyses will be done on the ITT population. An independent statistician will conduct clinical data analysis with SPSS 24.0 software (SPSS Inc., Chicago, IL, USA). Kolmogorov–Smirnov test will be used to analyze data distribution, and Levene’s test will be used to analyze homogeneity of variance. The quantitative variables will be presented as mean and SD or median and interquartile, whereas qualitative measures will be reported as percentages with 95% CI. Analysis of variance (ANOVA) test will be used with Bonferroni post hoc comparisons for continuous variables. The independent-samples *t*-test or the Mann-Whitney *U* test for continuous variables and the chi-square test, Fisher exact test, or Kruskal–Wallis test for categorical variables will be used, when suitable. We will describe 24-h HRV using time-domain measurements. Time-domain indices of HRV quantify the amount of variability in measurements of the interbeat interval (IBI), which is the time period between successive heartbeats. These values may be expressed in original units or as the natural logarithm (Ln) of original units to achieve a more normal distribution [41]. Pearson's coefficient will be used for bivariate correlations. All the statistical significance threshold tests will be set to *p*<0.05 with a two-tailed test.

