## Methods/design

### Design and setting

The present study is a single-center, parallel-controlled, equivalence, randomized clinical trial, and a total of ninety-two patients with FD will be recruited. These patients will be randomly allocated into either the acupuncture group or the moxibustion group with a 1:1 ratio. The study period includes a 1-week baseline, 4 weeks of treatment, and another 4 weeks of follow-up. Clinical measurements will be performed at the baseline, at the end of the treatment, and at the end of follow-up, respectively. Neuroimaging scans will be performed at the baseline and the end of the treatment. More details of the study design are shown in Fig. 1 and Table 1.

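### No single primary test is named for SF-LDQ, and none of the listed tests conditions on the baseline score, so available precision is given up

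*Protocol article*

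**What the plan says.** The section Primary outcome measurements defines the endpoint: "Our primary outcome is the improvement of SF-LDQ after 4 weeks of treatment". The section Design and setting schedules the score before and after treatment: "Clinical measurements will be performed at the baseline, at the end of the treatment, and at the end of follow-up, respectively". Table 1 agrees, marking SF-LDQ at 1-wk (baseline), 5-wk (end of treatment) and 9-wk (end of follow-up).

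The section Clinical data analysis gives the methods for continuous variables as a group:

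- Preliminary checks: "Kolmogorov–Smirnov test will be used to analyze data distribution, and Levene’s test will be used to analyze homogeneity of variance".
- One method: "Analysis of variance (ANOVA) test will be used with Bonferroni post hoc comparisons for continuous variables".
- Further methods, with suitability as the only rule for choosing: "The independent-samples *t*-test or the Mann-Whitney *U* test for continuous variables".
- Significance level: "All the statistical significance threshold tests will be set to *p*<0.05 with a two-tailed test".

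No sentence assigns one of these methods to the primary outcome. No baseline covariate, ANCOVA, regression or mixed model is mentioned for the clinical outcomes. The sample size rests on an unadjusted comparison of mean changes: "To achieve 90% statistical power (*α* = 0.05), at least 76 participants are needed".

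**The concern.** Two things are at stake.

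First, the primary comparison is not fixed. Three methods are available for the same variable and the rule for choosing among them is open. They do not all answer the same question: Mann-Whitney does not estimate the difference in mean improvement (2.06 points) on which the sample size is built.

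Second, the baseline score is used at most by subtraction. Subtracting the whole baseline is the most efficient use of it only in a special case. When the correlation between visits is below 1 and the standard deviations are equal, subtraction removes more of the baseline than the data warrant and adds noise to the treatment difference. ANCOVA estimates how much to remove. The cost of not using it is a wider confidence interval and lower power from the same patients.

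**Working it through.** **Inputs from the section Sample size calculation.** Mean change −5.62 (SD 2.81) with acupuncture and −3.56 (SD 2.62) with moxibustion; d = 0.758; two-sided α = 0.05; power 90%; 76 participants before attrition; 92 recruited (46 per arm); 20% attrition.

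**Not in the document, so assumed.** The correlation r between baseline and end-of-treatment SF-LDQ, and the SDs s0 (baseline) and s1 (end of treatment).

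**Step 1: the plan's own figure.**

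- Difference in mean change: 5.62 − 3.56 = 2.06.
- Pooled SD of change: √((2.81² + 2.62²)/2) = 2.717.
- d = 2.06/2.717 = 0.758, as stated.
- The two-sample t-test formula (noncentral t) gives 37.53 per arm, rounded up to 38, so 76 in total, as stated. Power at 38 per arm is 90.3%.
- With 20% loss from 46 per arm, 46 × 0.8 = 36.8 per arm remain, and power is 89.4%.

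**Step 2: ANCOVA against the change score.** Per-patient variances:

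- Change score: s0² + s1² − 2r·s0·s1
- ANCOVA: s1²(1 − r²)
- Difference between them: (s0 − r·s1)², which is never negative.

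With s0 = s1 the ratio is (1 − r²)/(2(1 − r)) = (1 + r)/2. The effective standardised difference becomes 0.758/√((1 + r)/2).

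| r (assumed) | Variance ratio | Saving | Power at 36.8 per arm, d = 0.758 | 95% CI half-width at 38 per arm (points) |
|---|---|---|---|---|
| change score | 1 | – | 89.4% | 1.24 |
| 0.3 | 0.65 | 35% | 97.8% | 1.00 |
| 0.5 | 0.75 | 25% | 95.9% | 1.08 |
| 0.7 | 0.85 | 15% | 93.6% | 1.15 |
| 0.9 | 0.95 | 5% | 90.8% | 1.21 |

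**Step 3: unequal SDs.** Take r = 0.6 and s0/s1 = 0.7, with s1 = 1. Change-score variance is 0.49 + 1 − 2 × 0.6 × 0.7 = 0.65. ANCOVA variance is 1 − 0.36 = 0.64. The saving is 0.01/0.65 = 1.5%. It is zero when s0 = r·s1. When s0 exceeds s1 it is larger than in the table.

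**Step 4: simulation check.** Normal data, equal SDs, 38 per arm, 8000 runs per scenario, r = 0.3, 0.5 and 0.7. Power was about 90% for the t-test on change and 88–89% for Mann-Whitney on change. For ANCOVA it was 98%, 96% and 94%. Type I error was 4.6–5.0% for all three methods.

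**The case against.** The strongest reply is that nothing here is wrong. The endpoint is a change score, the trial is powered for exactly that comparison, and each listed test holds its error rate. That stands. A reader might infer that the planned comparison is biased because chance baseline imbalance is handled imperfectly. The document does not support that charge: over randomisation, the difference in mean change is unbiased.

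A second reply is that the size of the gain depends on r and on the visit SDs, neither of which is given. That also stands, and is why the range runs from near zero upwards.

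Third, a reader might infer that the Kolmogorov–Smirnov result decides which test is used. The article says only "Kolmogorov–Smirnov test will be used to analyze data distribution" and leaves the choice of test to suitability. A link is the natural reading, but it is not written, and the check may serve equally to choose between mean and median summaries. It would be wrong to present a normality gate as a stated rule.

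Fourth, the Bonferroni step could be called empty because there are only two arms. But the questionnaires are taken at three or four visits, so the step may refer to comparisons across visits, where there are pairs to correct. It has nothing to correct only in the single between-arm comparison.

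Finally, a journal article condenses, and covariates are often left to the analysis plan. This has some force against reading silence as a decision never to adjust. It does not remove the point, because the article itself names the methods, and those methods leave baseline out. If the ANOVA is meant as repeated measures, its group-by-time test over baseline and end of treatment equals the change-score t-test, so that reading brings in no baseline covariate either.

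**Conclusion.** The point holds as an improvement to a valid plan, not as an error in it. The article lists several tests for continuous variables without naming the primary one for SF-LDQ, and none conditions on a baseline score that is already scheduled. The unadjusted change-score comparison is sound, and 76 participants suffice for it at the assumed effect.

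What is lost is precision. On the equal-SD assumption the loss is material at low to moderate correlation and small near r = 0.9. With unequal SDs it may almost vanish or be greater. That the primary test is undesignated can be read directly from the text; the size of the gain is conditional on figures the document does not give.

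**What to change.** In Clinical data analysis, name one primary analysis: ANCOVA of SF-LDQ at the end of treatment (5-wk in Table 1) on treatment arm, with baseline SF-LDQ as covariate, reporting the adjusted mean difference with its 95% confidence interval. Keep Mann-Whitney as a sensitivity analysis only. State that the choice of primary test does not depend on the distribution check, and that Bonferroni does not apply to the single two-arm comparison. If Bonferroni is meant for comparisons across visits, say so. Use the same baseline-adjusted model for the other continuous outcomes measured at baseline (NDI, SID, SAS, SDS and HRV, the last on the log scale where the plan uses it).

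The cost is wording. The baseline data are already scheduled, the named software (SPSS) fits ANCOVA, and no change to the sample size is needed.
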